### Using ML for CPMs

Various related work showed that AI approaches based on medical input data can result in accurate and robust statistical models to predict patient outcomes [30-34]. For example, supervised tree-based ML algorithms, for example, RF and Extreme Gradient Boosting, have shown promising results for classification tasks for posttransplant risks, for example, for graft failure, patient survival, or graft loss within a certain time period [35-40]. However, most of the existing approaches were research-driven and had only limited access to real-world medical data for their work, for example, using the Scientific Registry of Transplant Recipients data set [41]. Loupy et al [42] developed a risk score for kidney transplant recipients in context of a multicenter study making use of multivariable Cox regression analysis to predict graft loss in patients. Among others, they incorporated the following features: estimated glomerular filtration rate, proteinuria, histology, and HLA antibody [42]. Furthermore, recently advanced approaches based on neural networks making use of large proteomic databases occurred for assessment of immunogenicity and probability to generate antibodies [27,43,44].

From a clinical perspective, NephroCAGE aims to prevent the occurrence of adverse posttransplant end points, for example, loss of function, graft failure, and patient death. Nowadays, regular monitoring is applied to help identifying individual risk factors as early as possible. The use of digital patient records in hospitals for more than a decade provides the data foundation for our work because they form a longitudinal database of historic patient cases, medical decisions, therapies, and disease progression. Today, historical case data are only rarely used for current patient care. Our research hypothesis is that the analysis of historical cases can help to derive prognostic predictions for the individual patient risk to reach severe clinical end points. Based on the analysis of patient-specific parameters, a current patient case will be assigned to a group of similar, historic patient cases.

We will use the existing real-world data from historic patient cases from our clinical partners as a foundation for the definition of specific CPMs per clinical end point of interest [45,46]. Together with our clinical experts, we have defined specific CPMs to predict selected short- and long-term posttransplant events, for example, transplant failure and organ rejection. For example, a CPM trained for prediction of graft failure will cover whether this event will happen (yes or no) within 1 year (short-term) or 5 years (long-term). Such a CPM will predict a floating-point probability *p* ∈ [0*,*1], which will be mapped to positive and negative outcome classes. We will minimize the complexity of CPMs by incorporating the principle of data economy, that is, we will only use a minimal set of clinical parameters required to achieve a stable prediction quality. Therefore, we will make us of automatic and manual feature selection approaches to identify most descriptive features for the specific end point from the provided input data set [48-50]. Among others, our CPMs will make use of the following input parameters: recipient and donor data, laboratory values, biopsy results, medication, hospitalization records of the recipient, and HLA compatibility score. Recipient data include sex, weight, height, age at transplantation, end-stage kidney disease, HLA compatibility data, age at graft failure, cause of graft failure, age at death, and many others. Different kinds of follow-up data, for example, weight, and blood pressure, as well as laboratory values, for example, serum creatinine and daily protein-urea. In the case of kidney rejection or failure, a biopsy is performed and analyzed by a pathologist. For interpretation of renal allograft biopsies, Banff classifications are also available in the NephroCAGE data set.

Once a CPM has been trained at a clinical site, it will be shared with other clinical partners in Canada and Germany for validation and continuous training. CPM release versions will be packaged and deployed for execution to individual clinical sites using Docker containers. Thus, comparable small CPMs are exchanged whilst sensitive transplant data do not leave their protected clinical sites.

The current clinical transplantation process outlined in Figure 3 depicts multiple steps where prognostic predictions provided by NephroCAGE CPMs can support clinicians. In the following, we distinguish between pre- and posttransplant use of NephroCAGE CPMs: (1) pretransplant: the use of CPMs prior to transplantation can support more advanced genetic matching of donor and recipients and provide helpful insights for organ allocation; and (2) posttransplant: after transplantation CPMs can also incorporate patient-specific details on the graft function, for example, by including the latest prognosis, which provides a more specific view on the graft. We will focus on binary classifiers predicting short-term (1 year) and long-term (up to 8 years) outcomes post transplantation.

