## Introduction

End-stage kidney disease is growing globally affecting already up to 800 million (10%) people worldwide. Dialysis or kidney transplantation are current options for renal replacement therapy. There are 100,000 dialysis patients in Germany, and 50,000 in Canada [1,2]. In total, 1992 kidney transplantations in Germany and 1673 kidney transplantations in Canada were performed in 2021 [3,4]. Kidney transplantation is the preferred way of renal replacement therapy because it improves the quality of life for patients, extends life expectancy, and saves resources of the health care system [5-7]. However, there is a shortage in donor organs. As a result, in total 6593 patients in Germany and 3060 in Canada were on a waiting list for a suitable donor kidney in 2021 [4,8]. Despite the advances in medicine and improvement of short-term graft survival rates within the first year, long-term graft survival remains stagnant. It shows an attrition rate of approximately 5% annually after the second year resulting in reinitiation of dialysis or transplantation in approximately 50% of patients after 10 years [2,9]. After transplantation, regular follow-up visits especially in the first year are required to detect and prevent fatal outcomes, for example, infections, kidney rejections, or cancer due to over- or underimmunosuppression. Today, nephrologists lack adequate diagnostic measures for assessing and stratifying the individual patient’s risk for posttransplant outcomes, for example, graft failure or rejection [10]. Early detection of patients at high risk would open an additional prevention path: clinicians would have the opportunity to initiate countermeasures earlier and prevent fatal outcomes.

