Each clinical transplant center has to identify and extract relevant transplant data from their local HIS. Figure 2 depicts the involved process steps per category of data from top to bottom. After data extraction and format harmonization, the quality of retrieved data needs to be assessed by subject-matter experts. For example, selected cases need to be checked for inconsistencies in reported data. We will only address inconsistencies that occurred as part of the data extraction process. If data are confirmed to be inconsistent in the primary system, we have to exclude the patient case from further processing until these inconsistencies are addressed by the clinical transplant centers. Furthermore, outliers will also be removed from further processing.

**Table 1 table1:** Overview of the NephroCAGE data set: time period, covered years, number of patients, sex ratio, and age distribution. For MUHC^a^ and CHUM^b^ only patients consented Kidney Disease Biorepository–from Birth to Adulthood with first-time kidney transplant were included.

Items	NephroCAGE data set	Charité	UBC^c^	MUHC	CHUM
Period	1998-2020	1998-2020	2008-2018	2012-2019	2011-2019
Duration (years)	23	23	11	8	9
Patients	8067	4742	2510	415	400
[figure not shown] , n (%)	5081 (63%):2986 (37%)	2940 (62%):1802 (38%)	1606 (64%):904 (36%)	279 (67%):136 (33%)	256 (64%):144 (36%)
Age (years), mean (SD)	51*.*7 (14*.*3)	51*.*3 (14*.*0)	51*.*9 (15*.*3)	55*.*6 (12*.*4)	52*.*0 (12*.*8)

^a^MUHC: McGill University Health Centre.

^b^CHUM: Centre Hospitalier de l’Université de Montréal.

^c^UBC: University of British Columbia.

**Table 2 table2:** Categories of transplant data available within the NephroCAGE consortium.

Data category	Description	Selected examples
Recipient data	Measurements of patient data for transplant procedure	Weight, age, sex, HLA^a^ data, transplantation date, type of dialysis, time on dialysis, number of transplantations, delayed graft function, cold ischemia time, death date, DSA^b^, and MFI^c^ of DSA
Donor data	Measurements of donor data for transplant procedure	Weight, age, sex, and HLA data
Laboratory data	Laboratory values, for example, blood and urine	Creatinine, proteinuria (ratio and dip stick), albumin, and CRP^d^
Pathology reports	Medical pathology report	Rejection diagnosis, Banff lesion scores, and Banff diagnostic categories
Clinical notes	Information collected during clinical examination	Diagnoses, symptoms, medical history, physical examination, and written medications

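### Yes/no classifiers for outcomes up to 8 years do not fit the follow-up that the Table 1 periods allow: about 28% to 53% of patients cannot have 8 years, and the share differs strongly by centre

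*Protocol article*

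**What the plan says.** The section 'Using ML for CPMs' fixes the model class and the horizons. Its closing paragraph says: "We will focus on binary classifiers predicting short-term (1 year) and long-term (up to 8 years) outcomes post transplantation". Earlier in the same section, a graft-failure model is given as an example that "will cover whether this event will happen (yes or no) within 1 year (short-term) or 5 years (long-term"). The output is a probability, "which will be mapped to positive and negative outcome classes".

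Table 1 in 'NephroCAGE Data Set' gives, in the order all, Charité, UBC, MUHC, CHUM: "Period 1998-2020 1998-2020 2008-2018 2012-2019 2011-2019", "Duration (years) 23 23 11 8 9" and "Patients 8067 4742 2510 415 400".

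The article gives no date at which follow-up ends. 'Results' says that records had been retrieved by August 2023, so that is the latest cut-off it supports. 'Limitations' notes that the centres cover different periods, but treats this as a matter of era and changing practice and does not mention unequal follow-up. The first part of the Discussion calls the data longitudinally complete and gives no figure. Death dates are held, and death is named as an end point, but its role in a graft-failure label is not described.

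**The concern.** A patient transplanted late in a centre's period, alive and event-free at the data cut, has no known 8-year status. A plain binary classifier must still label that patient 'no', drop the patient, or leave out everyone whose potential follow-up is too short. The first two rules distort the risk in opposite directions and the third loses data. The centres' periods end in different years and have different lengths, so the distortion or loss is not the same at each centre.

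That matters for three planned uses:

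- The probabilities feed a risk score that sorts patients into three risk groups.
- Models are retrained at one site after another, so label bias that differs by site enters the training.
- The data are also meant for comparing outcomes between Germany and Canada, where such bias would look like a real difference.

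**Working it through.** **Table 1 first.** 4742 + 2510 + 415 + 400 = 8067, as stated. Last year minus first year plus 1 gives 23, 11, 8 and 9 years, as stated.

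**Share who cannot reach the horizon.** Assume even accrual over a period of D years that ends at time b (for example, the start of 2021 for Charité). With follow-up cut-off L and horizon H, the share short of H is [H − (L − b)] / D, limited to 0-100%.

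Cut-off end of August 2023, H = 8:
- Charité: (8 − 2.67)/23 = 23.2%
- UBC: (8 − 4.67)/11 = 30.3%
- MUHC: (8 − 3.67)/8 = 54.2%
- CHUM: (8 − 3.67)/9 = 48.1%

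Weighted by patients, about 2278/8067 = 28%. With the cut-off at the end of each period the shares are 8/23, 8/11, 8/8 and 8/9, or about 4245/8067 = 53%.

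| Horizon, cut-off | Charité | UBC | MUHC | CHUM | All |
|---|---|---|---|---|---|
| 8 y, period end | 35% | 73% | 100% | 89% | 53% |
| 8 y, 1 Jan 2022 | 30% | 45% | 75% | 67% | 39% |
| 8 y, Aug 2023 | 23% | 30% | 54% | 48% | 28% |
| 5 y, period end | 22% | 45% | 63% | 56% | 33% |
| 5 y, Aug 2023 | 10% | 3% | 17% | 15% | 9% |

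At 1 year the shares are 4-13% with a period-end cut-off and zero with the two later cut-offs.

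**Effect of two simple labelling rules.** For illustration, take the same constant graft-failure hazard of 0.05 per year at every centre. This is prompted by the Introduction ("It shows an attrition rate of approximately 5% annually after the second year") but applied here from transplantation. Ignore death at first. The true risk is 1 − exp(−0.05 × 8) = 33.0% at 8 years and 22.1% at 5 years.

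Worked case, Charité, 8 years, cut-off August 2023. Patients with short follow-up have 2.67 to 8 years. Their mean event-free probability at the cut-off is [exp(−0.133) − exp(−0.4)] / (0.05 × 5.33) = 0.768.
- Coded 'no': 0.768 × 0.330 + 0.232 × (1 − 0.768) = 30.7%. (The first 0.768 is the share with full follow-up, 1 − 0.232; that it equals the mean event-free probability is a coincidence.)
- Event-free incomplete patients dropped: 0.307 / (1 − 0.232 × 0.768) = 37.4%.

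| Horizon (true risk), cut-off | Rule | Charité | UBC | MUHC | CHUM |
|---|---|---|---|---|---|
| 8 y (33.0%), Aug 2023 | coded 'no' | 30.7 | 31.2 | 28.7 | 29.2 |
| | dropped | 37.4 | 40.0 | 48.3 | 45.7 |
| 8 y (33.0%), period end | coded 'no' | 27.6 | 21.8 | 17.6 | 19.3 |
| | dropped | 38.7 | 54.4 | 100 | 72.1 |
| 5 y (22.1%), Aug 2023 | coded 'no' | 21.6 | 22.1 | 21.7 | 21.7 |
| | dropped | 23.6 | 22.6 | 25.0 | 24.7 |
| 5 y (22.1%), period end | coded 'no' | 19.8 | 17.3 | 15.5 | 16.2 |
| | dropped | 24.5 | 28.9 | 34.7 | 31.9 |

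The 100% at MUHC arises because nobody there has a full 8 years under that cut-off, so only failures keep a label.

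**Sensitivity.** Add an assumed death hazard of 0.02 and lower the graft-failure hazard to 0.03, so that the true 8-year risk is 19.8%. With the August 2023 cut-off, coding 'no' gives 17.2-18.7% and dropping gives 22.4-29.0% across centres. With the period-end cut-off the ranges are 10.5-16.6% and 23.2-60.0%. The direction and the difference between centres remain.

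**Death alone.** With full follow-up and hazards 0.05 and 0.02, the 8-year cumulative incidence of graft failure is (0.05/0.07) × [1 − exp(−0.56)] = 30.6%. Coding death with a functioning graft as 'no' reproduces it. Dropping those deaths gives 34.9%. A composite with death gives 42.9%, which is a different quantity.

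**The case against.** The article nowhere says that incomplete cases are coded 'no' or dropped. A reader might infer that follow-up and death are ignored and that the long-term risks will therefore be biased; the text is silent and does not support that. 'NephroCAGE Data Set' says each site wrote a study protocol covering cohort, exclusion criteria and AI methods, so a labelling rule may stand there. A binary classifier can also be valid, through censoring weights or restriction to full potential follow-up.

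It is also tempting to call the 'no' label for death with a functioning graft an error. It is not: it yields the correct cumulative incidence. Nor do 5 years and 8 years flatly contradict each other: 5 years is an example for one end point and lies within 'up to 8 years'.

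The size is unsettled as well. The starkest figures need a period-end cut-off and come from MUHC, which has 415 of 8067 patients (5%). At 5 years with follow-up to August 2023, coding 'no' shifts the risk by about 0.5 points or less.

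All of this stands as a limit on the claim. It does not remove the point. The article itself fixes the model class and the range of horizons, and its own Table 1 shows that a material share of patients cannot be labelled at 8 years under any cut-off tried. Restriction, the one plain rule without administrative-censoring bias, costs 28-53% of the patients. The discussion of differing periods does not touch this.

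**Conclusion.** The point holds as a poor fit between the chosen model form and the data, not as a stated biased analysis. At 8 years, 28% to 53% of the 8067 patients lack the potential follow-up, from 23-35% at Charité to 54-100% at MUHC. Plain yes/no labels then lead either to centre-dependent bias, down or up according to the rule, or to the loss of that share of patients. The 5-year horizon is much less affected if follow-up reaches August 2023 (9% short) but not if it stops with the periods (33% short). The 1-year models are little affected.

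The figures assume even accrual, constant and equal hazards, administrative censoring only, and that the Table 1 period is the period of transplantation. If it is the period of data coverage, the period-end figures apply. Loss to follow-up is not quantified in the article and would add to these shares.

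**What to change.** - For the long-term models, keep the planned classifiers but fit them with inverse-probability-of-censoring weights, or use the time-to-event form of the same tree methods (random survival forest, survival gradient boosting).
- Evaluate with censoring-adjusted discrimination, Brier score and calibration.
- For graft failure, treat death with a functioning graft as a competing event: an event-free 'no' at the horizon, neither dropped nor censored.
- State the follow-up cut-off date.
- State one long-term horizon per end point, the same at all centres, and reconcile the 5-year example with the 8-year upper limit in 'Using ML for CPMs'. Check the horizon against the cut-off: if follow-up stopped with the Table 1 periods, MUHC would have no patient observed to 8 years, and neither weights nor survival methods could supply that information from its own data.
- Add unequal follow-up to 'Limitations', beside era and practice.

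The cost is somewhat more analysis work, with standard routines, and wider intervals at the long horizon. No new data are needed, because event and death timing are already held.

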### Patient-Specific Risk Score

The use of patient-specific risk scores is well known in medicine, for example, Glasgow Coma Scale, acute physiology and chronic health evaluation, and sepsis-related organ failure assessment for intensive care patients [51-53]. Risk scores are often used to stratify patients at risk or to predict selected aspects for patient care. They are often designed to use multiple values, for example, latest observational and laboratory values, and combine them toward a single numeric value for a selected clinical outcome. When a patient has a follow-up appointment or encounters any complication, latest data can be incorporated to update the patient-specific risk score.

We aim to define a patient-specific risk score for selected posttransplant events to provide additional insights for nephrologists during posttransplant care. The risk score is a low-dimensional metric representing the overall risk of developing posttransplant complications and will contribute to steps B1, B2, and B4 of the clinical process outlined in Figure 3. It will be calculated by combining the outcome of multiple CPMs and additional patient-specific parameters into a single clinical parameter. Thus, it can support clinicians in continuously monitoring selected kidney function parameters or initiating adequate action as early as possible. Based on the risk score, we will be able to classify patients into low-, medium-, and high-risk patients comparable to a traffic-light schema. Patients classified as high-risk patients will require increased systematic monitoring to prevent complications as early as possible, whereas patients classified as low-risk patients are not expected to develop severe events in the near future. This helps to use the available clinical workforce more efficiently, especially in times of a shortage of skilled labor.

### NephroCAGE FLI

Figure 4 depicts the building blocks of the NephroCAGE FLI, that is, from bottom to top: local transplant data accessed by local FLI runtimes, a federation layer for exchange of CPMs and data, as well as AI-based model making use of the NephroCAGE FLI to support clinicians in gaining medical insights. Each NephroCAGE clinical partner will join the NephroCAGE FLI by installing and configuring a local NephroCAGE FLI runtime environment on a dedicated host. After transplant data have been extracted from local clinical systems and harmonized, the host running the local FLI runtime environment is granted access to the data. Afterwards, the training of CPMs can be performed on the local data set. Once a stable CPM version becomes available, it will be released for sharing between partners using the NephroCAGE FLI. As a result, pretrained CPMs can be exchanged via the NephroCAGE FLI to facilitate model training even across country borders.

We will use DLT such as an Ethereum blockchain network to have decentralized storage for communicating model updates and code between clinical transplant centers without the need for a dedicated central authority [54]. For support of model training, we will implement an institutional incremental learning approach, where members retrain models one after another and compare different collaborative learning mechanisms with each other [23]. The aggregation of model values is well-established for parameter-based approaches like neural networks. However, only limited research investigates the aggregation of tree-based or kernel-based approaches like RFs or support vector machines, which are relevant for the NephroCAGE use cases.

**Figure 4 figure4:**
[figure not shown]
Building blocks of the NephroCAGE FLI. From bottom to top: individual clinical transplant centers from Germany and Canada contribute with more than 2 decades of transplant data enriched by publicly available data, for example, population and research data. Data are only accessible through local runtimes of the NephroCAGE FLI per clinical site, enabling training and sharing of model results whilst keeping data protected. All local FLI runtimes are interconnected through a federation layer, for example, providing access to a data repository for sharing model code and a DLT persistence to store transaction data. The federation layer provides harmonized data access by exposing an API, for example, for training and deployment of AI models and site-spanning data analysis. The results of the CPMs can be assessed by subject-matter experts, for example, to derive patient-specific risk scores for severe posttransplant risks. AI: artificial intelligence; API: app programming interface; CA: Canadian; CPM: clinical prediction model; DE: German; DLT: distributed ledger technology; FLI: federated learning infrastructure.

### Deployment and Integration Into Clinical Information Systems

An expert-facing web app will be developed by the consortium as clinical demonstrator. It will be designed using a representation state transfer (REST) API, which allows integration into existing clinical information systems, for example, T-Base at Charité [55]. The NephroCAGE clinical demonstrator will be used by clinicians to gain insights into patient-specific risk scores including additional information for prospective treatment. Therefore, selected data about individual patients will be exchanged with the CPM to calculate the individual probability for posttransplant risks. As a result, we will provide our CPMs in a local deployable way, that is, the CPMs will be executed by the clinical partners, to preserve privacy of any kind of patient data. Furthermore, the clinical demonstrator will serve as an evaluation platform to identify features that can be intervened in to improve outcome.

To facilitate the integration into existing clinical IT infrastructures, we will follow widely adopted internet protocols (HTTP and HTTPs) and well-known software development paradigms for the development of our CPMs and the clinical demonstrator. Therefore, we will develop the NephroCAGE CPMs as modular software components in Python providing an open API to expose their provided functionality for integration into existing software systems. Thanks to the API of the CPMS, the incorporated programming language and software stack remains transparent for the use of the client app. Through the API a stable software interface describing the required in- or output parameters is available, which will facilitate the integration into our clinical demonstrator and other existing clinical software systems. The REST software paradigm guides the development of web app upon established internet protocols [56]. Hence, RESTful APIs could be designed independent of the existing system with which they will be integrated, making them highly decoupled and modular. We will make use of REST API in our CPM design because it will build on well-established communication protocols for exchange of messages and therefore facilitates the integration into existing clinical IT systems. The execution environment for CPMs requires a diverse set of software dependency to function. Virtualization tools, such as Docker (Docker), can support the packaging of CPM software code, automatically install required software dependencies, and improve software deployment reducing maintenance efforts and hospital IT staff [57]. Thus, our CPMs will be packaged using a Docker container, which reduces deployment and maintenance efforts per clinical site.

